### {8 & 13} Trial design and timeline

After enrollment and screening assessment, 100 PD subjects will be randomly assigned (parallel assignment) in a 1:1:1:1 ratio to TIMP-RHY (25 people), or OT (25 people), or TIMP-NR (25 people) groups, or to wait for 5 weeks (Waitlist control group; 25 people). All PD subjects will undergo a magnetoencephalography (MEG) scan and a battery of tests before and after the TIMP-NR, TIMP-RHY, OT intervention, or twice separated by a 5-week period free of intervention (waitlist control group). First, to capture neural network and neurophysiological changes, participants will perform an MEG scan which engages them in an auditory-motor task. Then, clinical measures will be based on standardized PD neurologic assessments via the Unified Parkinson’s Disease Rating Scale [1], and fine motor assessments will include the Grooved Pegboard Test and finger-thumb opposition tests. Last, to capture changes in quality of life (QOL), we have included the 39-Item Parkinson's Disease Questionnaire (PDQ-39) [22]. The total duration of participation is 5–7 weeks (see the study flowchart in Fig. 1).

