### {14, 20a-c} Statistical methods and sample size

To address our primary mechanistic question, group comparison of mean Granger spectra changes using a linear mixed model controlling for sex and age will be analyzed during cued rhythmic tapping between regions of interest (ROIs: auditory, motor, precuneus, supramarginal gyrus and others) and corrected for multiple comparisons using the FDR method on the overall set of comparisons, *q* < 0.1. Statistically significant changes in Granger causality between ROIs are expected in the TIMP-RHY group but not in the OT or TIMP-NR groups due to the reliance on other motor networks, specifically those affected by PD pathology during fine motor training. A sample size per group of 25 subjects will allow us to determine between group differences with an effect size of 0.8 standard deviations/mean with 80% power and 0.05 significance, which is comparable to other studies examining neurophysiologic mechanisms of therapeutic interventions [31, 32] including similar studies using Granger causality as main outcomes in PD [33, 34]. We will perform exploratory analyses using linear regression to determine if any particular Granger feature is (1) associated with sex, age, or disease duration or severity and (2) more or less prone to motor function benefits. Based on our hypothesis, we predict fine motor training during TIMP-RHY, TIMP-NR, and OT will increase cortical motor beta and normalize gamma oscillations during the auditory-motor task in the MEG, although changes are expected to be stronger in the TIMP-RHY than in the OT and TIMP-NR groups. A 3 × 2 (group by frequency) mixed model ANOVA will be assessed to test this prediction.

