We will address our clinical research question by determining whether there is a significant change in fine motor skills following TIMP-RHY, TIMP-NR, and OT due to fine motor training compared to the non-therapy condition. We predict that TIMP-RHY will decrease mean GPT scores to a higher extent than the TIMP-NR and the OT groups. We will use an ANOVA F-test model to test this prediction on the mean GPT score change as well as pairwise contrasts with Tukey-Kramer correction for multiple comparisons to assess where the differences are. We do not expect such changes in the waitlist group due to the absence of fine motor strengthening. Given the large effect size of 0.8 sd/mean seen in other PD studies using the GPT grooved pegboard test as main outcome [35, 36], we anticipate that our sample size of 25 per group will allow us to determine a group difference of 15% decreased time using the dominant hand and to be comparable to published data [37]. We will also perform exploratory analyses using regression modeling to assess whether (1) sex, age, or disease severity and (2) cortical motor beta power changes are correlated with fine motor tests performance.

We will address our QOL research question by assessing changes in the PDQ-39 and CGI-I scales. As fine motor skills may improve, we expect a decrease in mean total scores (the higher the scores the higher the problems with quality of life, depression/anxiety and how things have changed) after a 5-week TIMP-RHY session and to a lower extent after OT or TIMP-NR sessions. We do not expect a change of QOL mean scores in the waitlist group.

Only complete sets of data (including both pre and post) will be included in the analysis. No imputation or other methods for handling missing data will be used during the analysis process.

No interim or subgroup analyses will be performed.

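### The Grooved Pegboard sizing statement mislabels its effect size, gives no SD to support the 15% figure, and claims power for an uncorrected comparison rather than the planned Tukey-Kramer contrasts

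*Protocol article*

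**What the plan says.** All of this is in the protocol article, section {14, 20a-c}, unless noted.

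- **Mechanistic outcome (Granger causality):** the stated inputs are "effect size of 0.8 standard deviations/mean with 80% power and 0.05 significance". The claim made from these inputs is "A sample size per group of 25 subjects will allow us to determine between group differences".
- **GPT, primary motor outcome:** "Given the large effect size of 0.8 sd/mean seen in other PD studies using the GPT grooved pegboard test as main outcome", from which the article concludes that "our sample size of 25 per group will allow us to determine a group difference of 15% decreased time using the dominant hand".
- **Analysis:** an ANOVA F-test on mean GPT change, followed by pairwise contrasts with Tukey-Kramer correction.
- **Predictions:** "TIMP-RHY will decrease mean GPT scores to a higher extent than the TIMP-NR and the OT groups". The waitlist group is not expected to show such changes.
- **Design (section {8 & 13}):** "100 PD subjects will be randomly assigned (parallel assignment) in a 1:1:1:1 ratio", so four groups of 25.

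The article gives no GPT mean, SD, SD of change or coefficient of variation. It does not say which contrast the 0.8 refers to.

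**The concern.** Three things do not fit together.

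1. The unit given for the effect size, in both places, is that of a coefficient of variation and not of a standardised difference.
2. The 15% is presented as following from 0.8, but turning SD units into a percentage needs an SD, and none is given.
3. The power figure is not for the analysis described. The group size matches a single uncorrected comparison, whereas the pairwise questions are to be answered with a correction over all pairs of four groups.

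The 15% is the only sizing statement in clinical units for the primary motor outcome. A reader who trusts it would expect roughly 80% power for the comparisons of TIMP-RHY with TIMP-NR and OT, and could take a non-significant result as evidence that rhythm adds nothing.

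**Working it through.** **Inputs from the article:** n = 25 per group, k = 4 groups, effect size 0.8, power 80%, significance level 0.05, claimed detectable difference 15%, Tukey-Kramer pairwise contrasts. The test's sidedness is not stated; two-sided is assumed.

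**Step 1. Reproduce the group size.** With 0.8 taken as a standardised difference d:

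n = 2(1.960 + 0.842)² / 0.8² = 24.5, rounded up to 25 per group.

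This matches exactly. One-sided testing would give 20. Exact power of the two-sample t-test with n = 25 (noncentrality 0.8 × √(25/2) = 2.83, 48 df) is 79%. So 0.8 works as a standardised difference for one uncorrected two-sided comparison.

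**Step 2. From 0.8 to 15%.** If d = 0.8 is to equal a 15% difference, then SD / mean = 0.15 / 0.8 = 18.75%. For other SDs, d = 0.15 / (SD / mean). The SDs below are assumptions on both sides of 18.75%, because the article gives none. Tukey-Kramer power is from Step 3.

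| Assumed SD of GPT change, % of mean | d for a 15% difference | Power, unadjusted | Power, Tukey-Kramer |
|---|---|---|---|
| 15 | 1.00 | 93% | 82% |
| 18.75 | 0.80 | 79% | 59% |
| 25 | 0.60 | 55% | 32% |
| 30 | 0.50 | 41% | 20% |

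**Step 3. The planned correction.** For four groups of 25 (96 error df), the Tukey-Kramer critical value on the t scale is the 95% point of the studentized range divided by √2, that is 3.70 / √2 = 2.61. The uncorrected t-test with 48 df uses 2.01. With noncentrality 2.83, power at 0.8 SD is about 59%. Solving for 80% power at n = 25 gives d of about 0.98. Even with an SD of 18.75% of the mean, the detectable difference would then be 0.98 × 18.75% = 18.4%, not 15%. Keeping 80% power at 0.8 SD would take about 38 per group.

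**Step 4. Contrasts between therapies.** Let R, C and W be the mean improvements on TIMP-RHY, a comparator therapy and waitlist. The article predicts R > C and no such change on waitlist. If C > W, then R − C < R − W. The article gives no size for R − C, so these are assumed values:

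| Assumed R − C (SD) | Power, unadjusted | Power, Tukey-Kramer |
|---|---|---|
| 0.3 | 18% | 6% |
| 0.4 | 28% | 12% |
| 0.5 | 41% | 20% |
| 0.6 | 55% | 32% |

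**The case against.** **The sample size is not miscalculated.** This stands. 25 per group follows from d = 0.8, and the article calls 0.8 a large effect size beside a power and a significance level. The label is wrong; the number was used as a standardised difference. A reader might take the label literally, put the SD at 80% of the mean, and conclude that 15% is only 0.1875 SD with about 10% power. The article's own group size rules that out: on that reading 447 per group would be needed for 15%.

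**The 15% may be right.** This also stands. The SD may be in the cited studies or a fuller protocol, and the SD of change could be below 18.75% of the mean; at 15%, power is adequate even with Tukey-Kramer. The figure is unsupported, not refuted.

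**The article does not apply 0.8 to every contrast.** Correct. A reader might infer that it does, or that 0.8 belongs to TIMP-RHY against waitlist. The text says neither; the defect is that no contrast is named. Nor does the sentence "changes are expected to be stronger in the TIMP-RHY than in the OT and TIMP-NR groups" help, since it concerns beta and gamma oscillations, not GPT.

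**The F-test comes first and may have adequate power.** It depends on the pattern: 82% if one group differs from the other three by 0.8 SD, but 63% for means of 0, 0.4, 0.4 and 0.8 SD. The F-test does not show which groups differ, and the prediction about TIMP-RHY rests on the pairwise contrasts.

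**The plan makes no equivalence claim.** True. The caution about non-significant results is a safeguard, not the correction of a stated error.

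**Conclusion.** The point holds as a mislabelled and incompletely supported sizing statement that does not match the planned pairwise analysis.

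- **Firm, given two-sided 0.05 and 25 analysed per group:** 0.8 gives 79% power for one uncorrected comparison but about 59% under the article's own Tukey-Kramer contrasts, where about 0.98 SD is detectable with 80% power.
- **Conditional:** the 15% holds at about 80% power, uncorrected, only with an SD of 18.75% of the mean. Over assumed SDs of 15% to 30%, power for 15% runs from 93% to 41% unadjusted and from 82% to 20% with Tukey-Kramer.
- **Conditional:** TIMP-RHY against TIMP-NR or OT has less power than TIMP-RHY against waitlist if the comparators improve at all. The 12% Tukey-Kramer power at 0.4 SD illustrates this and rests on an assumed gap. A reader might infer that the central prediction cannot be tested; the article gives no expected gap between therapies, so that goes too far.

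**What to change.** In section {14, 20a-c}:

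1. State 0.8 as a standardised difference in dominant-hand GPT change, and remove the division by the mean in both places.
2. Give the SD, with its source, that converts 0.8 SD to a percentage, and restate the detectable percentage from it.
3. Name the contrast to which the 0.8 applies.
4. Restate power under Tukey-Kramer: about 59% at 0.8 SD, or about 0.98 SD detectable with 80% power, at 25 per group.
5. Report TIMP-RHY against TIMP-NR and against OT as estimated differences with 95% confidence intervals, and state that a non-significant contrast will not be read as no difference.

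The cost is wording and a less favourable stated figure. Enrolment and the planned tests do not change.

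### The 25 per group claimed for the pegboard fits one unadjusted two-group test; each planned four-group Tukey-Kramer contrast has about 59% power at 0.8 SD

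*Protocol article*

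**What the plan says.** All references are to the protocol article.

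- **Design** (section {8 & 13}): "100 PD subjects will be randomly assigned (parallel assignment) in a 1:1:1:1 ratio", which is 25 in each of TIMP-RHY, TIMP-NR, OT and waitlist.
- **Sizing, mechanistic outcome** (section {14, 20a-c}, first paragraph): 25 per group is said to detect an "effect size of 0.8 standard deviations/mean with 80% power and 0.05 significance".
- **Sizing, pegboard** (same section, second paragraph): "Given the large effect size of 0.8 sd/mean seen in other PD studies using the GPT grooved pegboard test as main outcome", the protocol anticipates that "our sample size of 25 per group will allow us to determine a group difference of 15% decreased time using the dominant hand". This paragraph gives no power or significance level of its own.
- **Analysis, pegboard** (same paragraph): an ANOVA F-test on mean change, with "pairwise contrasts with Tukey-Kramer correction for multiple comparisons to assess where the differences are".
- **Questions to be answered** (same paragraph): change "following TIMP-RHY, TIMP-NR, and OT due to fine motor training compared to the non-therapy condition", and a prediction that TIMP-RHY lowers scores more than TIMP-NR and OT do.
- **Analysis set** (same section): "Only complete sets of data (including both pre and post) will be included in the analysis", without imputation.

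**The concern.** The sample-size statement and the rule for declaring group differences stand in the same paragraph and do not match. The clinical questions are pairwise: rhythm against no rhythm, rhythm against OT, and each therapy against waitlist. The Tukey-Kramer contrasts answer them, and they use a stricter critical value than the single two-group test that reproduces 25 per group. The number randomised also equals the number powered, while only complete pre/post sets are analysed, so nothing is held back for loss.

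The main risk lies in how a null result is read. A non-significant contrast between TIMP-RHY and TIMP-NR could be taken as evidence that rhythm adds nothing, in a trial believed to have 80% power for that comparison.

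**Working it through.** **Inputs from the protocol.** n = 25 per group; four groups; effect 0.8; power 80% and significance 0.05 (stated for the mechanistic outcome); target 15% shorter time with the dominant hand; Tukey-Kramer contrasts; complete cases only.

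**Assumptions.** The test is two-sided; sidedness is not stated, and a one-sided test would give 87.4%, which does not match. The effect is read as 0.8 SD. The protocol's unit, SD over mean, is unclear, but 0.8 SD is the reading that reproduces its figure.

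**Step 1. Reproduce the stated figure.** For two groups of size n, the noncentrality is δ = d·√(n/2) = 0.8 × √12.5 = 2.828.

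- Normal approximation: n = 25 per group, power 80.7%.
- Two-sample t, df = 48: 79.1%.
- Two-group contrast with pooled error, df = 4 × 24 = 96, unadjusted: 80.0%.

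So 25 per group is right for one unadjusted comparison with nobody lost.

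**Step 2. The planned pairwise test.** A Tukey-Kramer contrast is significant when |t| exceeds q(0.95; k, df)/√2. Power comes from the noncentral t with the same δ = 2.828.

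| Family | df | Critical \|t\| | Power per contrast at 0.8 SD |
|---|---|---|---|
| Four groups | 96 | 3.698/√2 = 2.615 | 58.6% |
| Three therapy groups only | 72 | 3.384/√2 = 2.393 | 66.8% |

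The four-group critical value corresponds to a per-contrast two-sided level of about 0.0104. Four groups is the natural family, because the protocol also compares the therapies with waitlist.

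**Step 3. The directional prediction.** If TIMP-RHY is better than TIMP-NR and than OT by 0.8 SD each, both four-group Tukey contrasts are significant in about 43% of simulated trials (0.426).

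**Step 4. Detectable difference.** Solving for d at 80% power with n = 25 and critical value 2.615 gives 0.98 SD. If 15% equals 0.8 SD, the implied SD is 15/0.8 = 18.75% of the mean, and 0.98 × 18.75% = 18.4%. About 38 completers per group would be needed for 80% at 0.8 SD. That number only shows the size of the gap; it is not a request.

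**Step 5. The omnibus F-test.** With noncentrality λ = n·Σ(μᵢ − μ̄)², df = 3 and 96, critical F = 2.70, and a largest pairwise gap of 0.8 SD:

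| Pattern of means (SD units) | λ | Power |
|---|---|---|
| Other two groups midway (0.8, 0.4, 0.4, 0) | 8 | 63.4% |
| One group differs from three (0.8, 0, 0, 0) | 12 | 82.4% |
| Two against two (0.8, 0.8, 0, 0) | 16 | 92.4% |

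**Step 6. Dropout.** The protocol gives no rate, so these losses are assumptions. The Tukey figures are per contrast over four groups.

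| Completers per group | Unadjusted t | Tukey |
|---|---|---|
| 25 | 79.1% | 58.6% |
| 22 | 73.6% | 51.6% |
| 20 | 69.3% | 46.6% |

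**The case against.** **The F-test is planned too.** The protocol names the ANOVA F-test as the test of its prediction and adds the contrasts to locate differences. If TIMP-RHY alone differs from the other three groups by 0.8 SD, the F-test has 82% power. This stands. A reader might infer that 25 per group supports nothing beyond one unadjusted two-group test, and the documents do not bear that out. But the F-test reaches 80% only under some patterns of means, the protocol names none, and a significant F does not show that TIMP-RHY is better than TIMP-NR or OT.

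**The 80% is not stated for the pegboard.** This also stands. A reader might take the pegboard claim to be an explicit 80% that is really 59%. The 80% appears with the mechanistic outcome, and the pegboard paragraph reuses the same n and effect size without restating power. The inference is reasonable, but it remains an inference.

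**The arithmetic is not wrong.** Correct: 25 per group reproduces. The fault is that the basis for sizing differs from the planned contrasts.

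**Retention is addressed.** Make-up sessions, weekly calls and free rides are planned over a short participation of 5 to 7 weeks, so loss may be small. However, the retention plan itself expects motivation to decline, and the 59% assumes no loss at all.

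**The unit is unclear.** Taken literally as an SD that is 0.8 of the mean, a 15% difference would be 0.15/0.8 = 0.19 SD, with about 10% unadjusted power. A reader might conclude that the trial is hopelessly small. That reading does not reproduce the protocol's own sizing, so the unit is better treated as needing clarification.

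**Detail left elsewhere.** The SD behind the 15% may be in the full protocol or the cited studies. That excuses its absence from an article. It does not remove the mismatch between the stated sizing and the stated contrasts.

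**Conclusion.** The point holds in a bounded form. The sizing carried over to the pegboard corresponds to one unadjusted two-sided comparison with all 25 per group analysed. For the pairwise questions the protocol asks, the planned Tukey-Kramer contrasts have about 59% power each at 0.8 SD, roughly 20 points below the figure paired with the same n and effect size for the mechanistic outcome. The shortfall is smaller (67%) if only the therapy groups form the family. It is larger (about 43%) for the joint claim against TIMP-NR and OT.

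These results rest on reading the effect as 0.8 SD, two-sided testing, equal variances and no dropout. The 18.4% figure further assumes that 15% equals 0.8 SD. The planned analysis itself remains valid, since Tukey-Kramer controls the type I error. What is wrong is the claim about what 25 per group can determine, and hence how a non-significant contrast would be read.

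**What to change.** In section {14, 20a-c}, pegboard paragraph:

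1. State power and detectable difference for the four-group Tukey-Kramer contrasts. With 25 completers per group, these are about 59% at 0.8 SD and about 0.98 SD at 80% power.
2. If the F-test is to carry the sizing, state its power with the assumed pattern of means.
3. Base both on the expected number of completers, and state the dropout assumed.
4. Clarify the unit of the 0.8 effect size and give the SD that links it to 15%; 18.75% of the mean is implied.

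The contrast set should stay as it is. Restricting it to TIMP-RHY against each other group would drop the comparisons of TIMP-NR and OT with waitlist that the protocol asks for.

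The cost is a change of text. No extra patients are needed. The stated figure becomes less favourable, and non-significant contrasts will have to be reported with that in mind.

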Quality of life (QOL) outcome measures will include the 39-Item Parkinson's Disease Questionnaire (PDQ-39) [22] and the Clinical Global Impression—Improvement Scale (CGI-I) to better define meaningful self-report and clinical changes. As an exploratory QOL outcome, we will include the Hospital Anxiety and Depression Scale (HADS) [29, 30] to assess for potential improvements in depressive symptoms and anxiety, which may improve with fine motor therapies.

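### CGI-I is already a rating of change, but the protocol treats it as a status score with a pre-to-post change; it should be analysed as a single post-visit rating

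*Protocol article*

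**What the plan says.** All places are in the protocol article.

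- Section {12} Outcomes lists, beside PDQ-39, the "Clinical Global Impression—Improvement Scale (CGI-I) to better define meaningful self-report and clinical changes".
- Section {14, 20a-c} Statistical methods and sample size handles the two scales together, by "assessing changes in the PDQ-39 and CGI-I scales". On direction it states that "we expect a decrease in mean total scores" after TIMP-RHY, with a smaller fall after OT or TIMP-NR. For the control arm it adds: "We do not expect a change of QOL mean scores in the waitlist group".
- The same sentence explains that higher scores mean more problems with quality of life, "depression/anxiety and how things have changed". Of the scales involved, only CGI-I fits the last part of that phrase.
- The section then sets a general rule: "Only complete sets of data (including both pre and post) will be included in the analysis". It rules out imputation. Section {18a-b, 19, 29} Data collection, management, and accessibility repeats the complete-pairs rule. Neither place exempts CGI-I.
- Section {8 & 13} Trial design and timeline schedules "a battery of tests before and after the TIMP-NR, TIMP-RHY, OT intervention", or twice five weeks apart for the waitlist arm. The measures it names are MEG, UPDRS, the Grooved Pegboard, finger-thumb opposition and PDQ-39. CGI-I is not among them.

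**The concern.** PDQ-39 measures a state. It can be taken at two visits and differenced, and a fall in its mean has a plain meaning. An improvement scale records how the patient has changed since some earlier point, so the comparison with baseline is already inside the score. Before therapy starts there is nothing to compare with, and the article defines no reference point for such a rating.

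Followed as written, the plan leads to one of two places:

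- **A baseline CGI-I is collected.** It is then either a constant (everyone rated as unchanged) or a value without a defined meaning that is subtracted from the informative post-visit rating. Anyone with a valid post rating but no baseline rating is dropped.
- **No baseline CGI-I is collected.** No participant has a complete CGI-I pair, and the inclusion rule read literally removes the outcome altogether.

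At stake are the meaning of the within-arm result and possibly the precision of the between-arm comparison, for one quality-of-life outcome.

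**Working it through.** **Step 1. Reproduce the plan's own figure.** The article gives 25 per group for a difference of 0.8 SD, 80% power and a significance level of 0.05. Sidedness is not stated; two-sided is assumed.

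n per group = 2 × (1.960 + 0.842)² / 0.8² = 2 × 7.85 / 0.64 = 24.5, rounded up to 25.

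The figure reproduces. Power at 25 per group is 0.807 by the normal approximation and 0.791 by the two-sample t-test. The 0.8 SD is stated for the Granger and Grooved Pegboard outcomes, not for CGI-I. It serves below only as a yardstick.

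**Step 2. Is the between-arm contrast biased?** The expected difference in mean change between two arms is the expected difference in post ratings minus the expected difference in baseline ratings. Under randomisation the second term is zero, provided the baseline rating is not itself influenced by knowing the arm. The contrast therefore targets the same quantity as the post-only comparison, and what can change is its variance.

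**Step 3. Effect on precision.** Set the SD of the post rating to 1. Let k be baseline SD divided by post SD, and ρ the pre/post correlation. The documents give neither, so both are assumptions.

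SD of (post − baseline) = √(1 + k² − 2ρk)

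Standardised effect = 0.8 / that SD

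Subtraction inflates the variance only when k² > 2ρk, that is, when ρ < k/2.

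| k | ρ | SD of difference | Standardised effect | Power, t-test, 25 per arm |
|---|---|---|---|---|
| 0 (constant baseline) | – | 1.000 | 0.800 | 0.791 |
| 0.5 | 0 | 1.118 | 0.716 | 0.698 |
| 0.5 | 0.2 | 1.025 | 0.781 | 0.772 |
| 0.5 | 0.5 | 0.866 | 0.924 | 0.893 |
| 1 | 0 | 1.414 | 0.566 | 0.500 |
| 1 | 0.2 | 1.265 | 0.632 | 0.591 |
| 1 | 0.5 | 1.000 | 0.800 | 0.791 |
| 1 | 0.7 | 0.775 | 1.033 | 0.947 |

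For k = 1 and ρ = 0: √(1 + 1 − 0) = 1.414 and 0.8 / 1.414 = 0.566. By the normal approximation, 50 per group would then be needed instead of 25.

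**Step 4. The within-arm change.** No arithmetic helps here. The quantity is a post-visit improvement rating minus an improvement rating with no stated comparator. A fall in its mean, or its absence in the waitlist arm, has no defined meaning except when the baseline is a constant. In that case it is just the post rating shifted.

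**The case against.** The best defence is that the wording is shorthand. Section {12} Outcomes shows that the authors know CGI-I captures change, so assessing changes in the two scales may mean change as each instrument records it. One summary sentence covers several scales: it mentions depression and anxiety, although that paragraph does not name HADS. The ANOVA on change and the Tukey-Kramer contrasts are stated for the Grooved Pegboard only. No test is fixed for the quality-of-life outcomes, and that detail may properly sit in an analysis plan that is not shown.

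Much of this stands. No baseline CGI-I is documented, no subtraction rule is written out for it, and the absence of a named test is not a finding. But the expected fall in means, the unchanged waitlist mean and the unqualified pairs rule all fit a status score and not a change rating. Even if the wording is only loose, an analysis plan that followed the text would carry the problem forward.

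A reader might be tempted to infer more, and the documents do not support it:

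- *Subtracting a baseline can only add noise.* A constant baseline adds none, and a correlation above k/2 reduces the variance.
- *The between-arm estimate is biased or meaningless.* Step 2 shows that its expectation is unchanged.
- *Power will drop to 50%.* That is the worst case tabulated, and it needs a baseline rating with full variance and no correlation with the post rating. Nothing in the article points to either.

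**Conclusion.** The point holds as a minor correction. The article handles an improvement rating as if it were a status score. A within-arm pre-to-post change in CGI-I is not interpretable, because the pre-therapy rating has no reference point.

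For the randomised between-arm contrast the issue is possible loss of precision. At an assumed 0.8 SD and 25 per arm, power runs from an unchanged 79% (constant baseline) down to 50% (equal variance, uncorrelated), and it rises above 79% if the correlation is strong. The whole range rests on assumed k and ρ and on an effect size that the article does not state for CGI-I. If no baseline rating is taken, precision is not the issue: the pairs rule read literally leaves nothing to analyse.

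CGI-I is neither the primary mechanistic nor the primary motor outcome, and it plays no part in the sample size. The trial's main conclusions do not depend on it.

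**What to change.** Amend section {14, 20a-c} Statistical methods and sample size as follows:

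1. State that CGI-I is rated once, at the post visit, relative to baseline (for the waitlist arm, after the five-week wait).
2. State that this post-visit rating alone is compared between the four arms.
3. Exempt CGI-I from the complete pre/post rule, both here and in section {18a-b, 19, 29}.
4. Reword the expectation as a lower post-visit CGI-I rating in TIMP-RHY than in the other arms.
5. Keep PDQ-39 as a change analysis.

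An ordinal method, such as a proportional-odds model or a Kruskal-Wallis test with pairwise follow-up, would be reasonable for the CGI-I rating but is not essential to the correction.

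The cost is a sentence or two of wording. No new data are needed and no other analysis is affected.

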### {18a-b, 19, 29} Data collection, management, and accessibility

MEG data collection is under the responsibility of a trained neurophysiology specialist to ensure data quality and assessment of unplanned data contamination. Motor scales and surveys are being collected by the study investigator who has been thoroughly trained by clinical and research colleagues during past clinical trials. Each measure and scale used in this study is widely used in the research community and has proven reliability and validity in the scientific literature. After collection, data is entered into the local Research Electronic Data Capture (REDCap) database, and data entry is verified by a research assistant non-affiliated to the study. Only complete sets of data (pre/post) will be included in the analysis. Study PI and statistician will have access to the final trial dataset.

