### Retention plan

We suspect that subject’s motivation and assiduousness might decline during the course of the 5 weeks. To prevent this, we will follow-up with the participants on a weekly basis via phone call to ensure proper completion of all the sessions. We will offer to arrange free rides via Access-a-Ride from participants’ homes to the therapy offices. If needed, we will modify some exercises to prevent possible patient difficulties with the current protocol.

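### The protocol fixes a complete-case analysis and forbids any missing-data method, so dropout related to both arm and outcome could bias the randomised comparison unseen

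*Protocol article*

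**What the plan says.** The rule appears twice in the protocol article. The data collection section (items 18a-b, 19, 29) says "Only complete sets of data (pre/post) will be included in the analysis". The statistical methods section (items 14, 20a-c) says "Only complete sets of data (including both pre and post) will be included in the analysis" and adds "No imputation or other methods for handling missing data will be used during the analysis process". It is not tied to one outcome, so it covers the MEG, Grooved Pegboard (GPT) and quality-of-life analyses.

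The primary motor test is an ANOVA on GPT change, with no covariates stated, followed by Tukey-Kramer contrasts. The mechanistic analysis is a linear mixed model for changes in Granger spectra, controlling for sex and age.

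On conduct, the blinding section says participants and therapists are not blinded. The randomisation section says participants are told their arm once the first research visit has been scheduled, that is, before baseline assessment. The three therapy arms have 15 sessions over five weeks; the waitlist arm has none. The retention plan expects that "motivation and assiduousness might decline during the course of the 5 weeks" and answers with weekly calls, free rides and modified exercises. The interventions section adds make-up sessions. No dropout rate is given.

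**The concern.** This is not a detail left to an analysis plan. The protocol sets a complete-case rule and excludes every alternative, so a later plan could add a check only by contradicting it.

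Randomisation protects the comparison of the groups as assigned. Once the analysis is confined to those who return, that protection depends on why the others did not. Participants know their arm, and the burden differs between therapy and waiting, so loss that differs by arm is foreseeable. If those who leave a therapy arm also tend to be its poorer responders, that therapy looks better than it is; the reverse pattern hides a benefit.

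Nothing planned would show either. The ANOVA uses completers only. The mixed model is applied to changes, and the complete-set rule removes anyone with a single visit. The retention measures lower the amount of loss but neither detect nor correct selection.

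**Working it through.** **Inputs from the protocol.** 25 per group, a difference of 0.8 SD, 80% power and 0.05 significance (statistical methods section: "A sample size per group of 25 subjects will allow us to determine between group differences with an effect size of 0.8 standard deviations/mean with" ... "with 80% power and 0.05 significance"). Four arms of equal size (trial design section: "100 PD subjects will be randomly assigned (parallel assignment) in a 1:1:1:1 ratio"). Sidedness is not stated; two-sided is assumed because it reproduces the stated 25, whereas one-sided gives 20.

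**Step 1: the plan's own figure.** n = 2(1.960 + 0.842)² / 0.8² = 24.5, so 25 per group. Power at 25 is Φ(0.8·√(25/2) − 1.960) = Φ(0.868) = 80.7% (79.1% with the t distribution). The stated size reproduces, and it leaves no allowance for missing data.

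**Step 2: dropout unrelated to outcome, equal in both arms of a pair (assumed rates).** Power = Φ(0.8·√(m/2) − 1.960), with m = 25(1 − d):

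| Loss d | m | Power |
|---|---|---|
| 0% | 25 | 80.7% |
| 10% | 22.5 | 76.5% |
| 20% | 20 | 71.6% |

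These figures are for one pairwise comparison, normal approximation, without the Tukey-Kramer correction. Keeping 25 complete cases per arm would need 25/0.9, so 28, at 10% loss, or 25/0.8, so 32, at 20%.

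**Step 3: dropout related to outcome, in one arm only (assumed).** Suppose a fraction p of one arm leaves, those lowest on a latent variable that has correlation ρ with the change score. The mean of those remaining shifts by ρ·φ(z_p)/(1 − p) SD. At p = 0.20, φ(0.842)/0.80 = 0.280/0.80 = 0.350 SD when ρ = 1. At ρ = 0.5 the shift is 0.175 SD, and at ρ = 0.3 it is 0.105 SD.

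A simulation gives the matching error rates: 20,000 runs, 25 per arm, true difference zero, no loss in the comparison arm, two-sided t-test at 0.05 on completers.

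| Loss in one arm | ρ | Bias (SD) | Type I error |
|---|---|---|---|
| 12% | 0.3 | 0.06 | 5% |
| 12% | 1 | 0.22 | 14% |
| 20% | 0 | 0.00 | 5% |
| 20% | 0.3 | 0.10 | 6% |
| 20% | 0.5 | 0.17 | 9% |
| 20% | 1 | 0.34 | 24% |
| 32% | 0.3 | 0.15 | 8% |
| 32% | 1 | 0.51 | 43% |

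The formula gives 0.35 and the simulation 0.34 at 20% loss and ρ = 1; the small difference comes from the finite arm size of 25. Against the 0.8 SD target, 0.105 SD is 13% and 0.35 SD is 44%.

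**Step 4: reading the table.** The row with ρ = 0 shows that loss in one arm alone leaves the contrast unbiased if it is unrelated to outcome. If two arms lose participants in the same way, the two shifts cancel in their contrast.

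**The case against.** The strongest reply is that the risk is modest. The intervention lasts five weeks and retention is actively managed. Waitlisted participants are assigned a therapy after their post visit, which gives them a reason to attend it. People whose insurance does not cover OT are excluded at entry, which removes one cause of arm-specific loss. The three therapy arms have equal session loads, so similar loss would largely cancel in the contrasts of TIMP-RHY with TIMP-NR and OT. The retention sentence concerns motivation to complete sessions, not missing outcome data. All of this stands and bears on how likely the problem is. None of it supplies a check.

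Four stronger readings are tempting, and the documents do not support them:

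- *Dropout that differs by arm is enough to bias the result.* It must also be related to outcome; otherwise only power is lost.
- *Change-score ANOVA on completers is biased whenever dropout depends on baseline severity or age.* The contrast is biased only if that covariate predicts change and the dependence differs by arm, or if the treatment effect varies with the covariate.
- *The bias will be near 0.35 SD.* That figure needs exactly the worst-responding fifth of one arm to leave and no such loss elsewhere. Nothing in the protocol points to that extreme.
- *A failed MEG scan deletes a valid GPT pair.* The protocol itself explains completeness as having both pre and post data. One clarifying sentence would settle the matter.

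Nor does any section exclude participants for missed sessions or deny the post visit to those who stop therapy.

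**Conclusion.** The concern holds as a risk that the plan has barred itself from examining, not as a demonstrated bias. Its size and direction cannot be known, because no dropout rate or pattern is documented. With 20% loss confined to one arm, the bias is about 0.10 to 0.35 SD and the type I error about 6% to 24% for ρ from 0.3 to 1; at 12% loss and ρ = 0.3 the effect is slight. Loss unrelated to outcome costs roughly 4 percentage points of pairwise power at 10% and 9 at 20%. The flaw is the explicit prohibition, which covers every outcome. It should be fixed; given the short follow-up and the retention effort, it does not by itself undermine the trial.

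**What to change.** - Delete the ban on missing-data methods in the statistical methods section, and amend the complete-set rule in both places.
- Analyse all randomised participants in their assigned arm, whatever number of sessions they attended, and outcome by outcome.
- Make the primary GPT model an ANCOVA on the post score adjusted for baseline GPT, age and sex, or an equivalent likelihood-based model using all available visits. This handles loss that depends on those covariates.
- Add one missing-not-at-random sensitivity analysis (delta-adjusted, taken to a tipping point), imputing from baseline data with a parsimonious model.
- Report missingness and its reasons by arm.
- Keep the unadjusted complete-case ANOVA as supportive.

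Multiple imputation by arm need not be the primary method. With 25 per arm the models may be unstable, and the other motor scores come from the same visit as the GPT, so they will usually be missing with it. Participants who withdraw on learning their arm have no baseline GPT; for them imputation has little to work with, and the tipping-point analysis carries the weight.

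The cost is a little more analysis work. No new visit, procedure or participant is needed, and the change should be made before the data are analysed.
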